#### Control group therapy

For the participants in the control group, all binocular visual function tests will also be completely performed at each follow-up visit. If refractive status changes, appropriate prescription will be provided and used in a pair of new glasses.

If only binocular visual function deterioration occurs, it is proposed that they continue to be observed; if accompanied by a small angle of exodeviation but not meeting the criteria of suboptimal surgical outcome or if participants ask for visual function therapy, they will have deviated from the study protocol and will be considered to be dropped out of group. If eye position regression is obvious and the definition of recurrence is reached, he or she will be classified as having a suboptimal surgical outcome. They will be offered a reoperation to align the eye position or start orthoptic therapy during the study.

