Before the start of each training, some simple binocular function tests will be performed, and the training program will be adjusted based on those test results. The patients can stop training in the hospital and maintain home training (15 min each day) to maintain efficiency if the test results showed that performance had reached or even exceeded the normal level. However, if a decrease in the test results is observed during the follow-up, the appropriate therapeutic treatment will be reinitiated. In addition, the home training is a computerized procedure for binocular vision therapy. Also, some will be asked for 1–2 times a week hospital-based training. For the results and purpose of our study, parents will be required to record the training in detail, including time, frequency, and simple training experience (e.g., difficult, easy, unwilling to do).

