### Criteria for dropout

The criteria of dropout will be (1) patients in orthoptic therapy group who did not accept training with 2 weeks of enrolment, (2) patients in control group who had started any kind of postoperative non-surgical treatment (e.g., patching, orthoptic training), (3) participants who had requested to be withdrawn from the study. All participants will be permitted to withdraw or terminate the study for any reason during the study, and the reasons will be recorded. Discontinuation or irregular orthoptic therapy will not be a reason for withdrawal from the study, and participants could complete follow-up visits provided if they are willing.

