### Sample size

Sample size calculation is based on the expected value of efficacy from previous studies. The proportion of participants meeting suboptimal surgical outcomes is 16.7% [20] in surgery combined with orthoptic therapy group and 36.5% in surgery alone [21]. We hypothesis that there will be a significant difference in the cumulative proportion of suboptimal surgical outcome at 24 months after surgery between our two groups. We set the statistical power was set at 80% with a type 1 error probability (alpha) of 0.05 based on a 2-tailed chi-square test. The theoretical sample size was 61, with a 1:1 sample ratio. After allowing for a maximum dropout rate of 10% during the 2-year follow-up, we found that the estimated the sample size for each group to reach a statistical significance was 68.

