### Statistical analysis

Statistical analysis will be performed using SPSS software version 20.0 (IBM Corp., Armonk, NY, USA). The parameters to be calculated are the means ± standard deviations for the continuous variables and the rates (proportions) for the categorical variables.

For the primary analysis, the cumulative proportion of participants meeting the criteria for suboptimal surgical outcomes by 2 years will be compared between the 2 groups using the Kaplan-Meier method. An intergroup difference and a corresponding 95% confidence interval (CI) will also be calculated. Each of the 2 individual components of the specified suboptimal surgical outcome criteria will be assessed using the chi-square test.

For all IXTs who completed the 24-month follow-up, changes in exodeviation measured by PACT, stereoacuity, exotropia control score, accommodative amplitude and facility, and fusional convergence amplitude between baseline and the 24 months will be compared between the two groups in linear regression models that will be adjusted for the corresponding baseline values. Additionally, considering that binocular visual function is different in different age, the final data may be divided into two subgroups according to different ages.

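### Arm-specific dropout rules tied to post-randomisation events, and stated inconsistently, expose the Kaplan-Meier comparison to informative censoring

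*Protocol article*

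**What the plan says.** Four places in the protocol article bear on this.

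- **Control group therapy.** Loss of binocular function alone means continued observation. But "if accompanied by a small angle of exodeviation but not meeting the criteria of suboptimal surgical outcome", or on a request for visual function therapy, such controls are treated differently: "they will have deviated from the study protocol and will be considered to be dropped out of group". Controls who reach the endpoint count as suboptimal outcomes and may then be treated.
- **Criteria for dropout.** Criterion (1) covers "patients in orthoptic therapy group who did not accept training with 2 weeks of enrolment". Criterion (2) covers "patients in control group who had started any kind of postoperative non-surgical treatment". Criterion (3) is withdrawal on request. Stopping therapy or doing it irregularly is expressly not a reason for withdrawal, and those children may complete their visits.
- **Intervention for the orthoptic therapy group.** A trained child whose function falls stays in: "if a decrease in the test results is observed during the follow-up, the appropriate therapeutic treatment will be reinitiated".
- **Statistical analysis.** The cumulative proportion with a suboptimal outcome by 2 years "will be compared between the 2 groups using the Kaplan-Meier method". The section does not say what becomes of children labelled dropouts.

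**The concern.** The endpoint is an exodeviation of at least 10 PD by SPCT or a loss of at least 2 octaves of stereoacuity. A small exodeviation together with loss of function is a step on the way there. Kaplan-Meier estimation assumes that a censored child has the same future risk as a child who stays under observation. A rule that removes controls because they show a precursor of failure breaks that assumption, and the therapy arm has no matching rule. Losing such controls lowers the estimated control failure rate and works against therapy.

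The other rule may push the opposite way. Therapy-group children who never start are removed, so the therapy arm may come to consist of the better-motivated families. The two effects need not cancel, and the documents give no basis for saying which is larger.

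The control trigger is also wide. Entry allows exodeviation below 10 PD by PACT, and a small angle is given no lower limit. A control with an unchanged entry-level deviation who then loses some function could be labelled a dropout.

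**Working it through.** **1. The rules side by side**

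| Event after randomisation | Control arm | Therapy arm |
|---|---|---|
| Function declines, no exodeviation | observed | training restarted, kept |
| Function declines with small exodeviation below the endpoint | dropout under Control group therapy; not listed under Criteria for dropout | no dropout rule |
| Asks for therapy | dropout under Control group therapy; not listed under Criteria for dropout | not applicable |
| Starts non-surgical treatment | dropout under Criteria for dropout | assigned treatment |
| Does not start assigned training in 2 weeks | not applicable | dropout |
| Irregular or stopped training | not applicable | kept |

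Rows 2 and 3 show the disagreement between the two sections.

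**2. The plan's own figures (Sample size)**

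Inputs: 36.5% v 16.7%, power 80%, "type 1 error probability (alpha) of 0.05", "based on a 2-tailed chi-square test".

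- The dropout step reproduces: 61 / 0.90 = 67.8, so 68 per arm. That leaves room for 68 − 61 = 7 dropouts per arm.
- The 61 does not reproduce as two-sided. With mean proportion 0.266, n = [1.96·√(2·0.266·0.734) + 0.842·√(0.167·0.833 + 0.365·0.635)]² / 0.198² ≈ 77. Replacing 1.96 by 1.645 gives 61. This is a separate matter. It matters here only because it explains why power starts below 80%.

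**3. Effect of losing pre-failure controls (fractions assumed; the documents give none)**

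Set-up: 68 per arm, 36.5% v 16.7%, failures first seen at 6/12/18/24 months in 35/25/20/20%, and losses in the control arm only. A dropped child is censored one visit before the failure would have been seen. The test is a two-sided z test of the 24-month Kaplan-Meier difference with Greenwood variance.

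Expected control failures are 0.365 × 68 = 24.8, which is 8.69, 6.20, 4.96 and 4.96 at the four visits. Suppose 20% of those due at 12, 18 or 24 months are dropped after the preceding visit:

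- Numbers at risk: 68; 68 − 8.69 − 1.24 = 58.07; 58.07 − 4.96 − 0.99 = 52.12; 52.12 − 3.97 − 0.99 = 47.15 (to rounding).
- Control estimate: 1 − (1 − 8.69/68)(1 − 4.96/58.07)(1 − 3.97/52.12)(1 − 3.97/47.15) = 32.5%.

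All scenarios, with power by simulation:

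| Would-be control failures dropped | Only after a scheduled visit: control KM, power | Also before 6 months: control KM, power |
|---|---|---|
| none | 36.5%, 76% | 36.5%, 76% |
| 20% | about 33%, about 60% | about 31%, 49% |
| 33%, plus 10% of non-failures | about 31%, about 48% | about 28%, 32% |
| 50% | 26–27%, 27–30% | 21–22%, about 10% |

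Repeat simulations move the power figures by a point or two. The ranges in the last row are without and with 10% of non-failures also dropped. A separate calculation with a constant hazard, and drops only after a visit, gives a control estimate of 34.4%, 31.1% and 25.1% for 10%, 25% and 50% dropped.

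**4. Against the dropout allowance of 7**

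- 20% dropped: 0.20 × 24.8 = 5.0 controls, or 0.20 × 0.65 × 24.8 = 3.2 if only after a visit. Both are below 7.
- 50% dropped: 12.4, or 8.1 if only after a visit. Both are above 7, before any ordinary loss to follow-up.

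**5. Non-starters in the therapy arm (assumed: 10% never start and carry the control risk)**

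If starters fail at 16.7%, the arm as assigned fails at 0.9 × 16.7% + 0.1 × 36.5% = 18.7%. Dropping non-starters would flatter therapy by about 2 points.

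**6. Bounds if 7 of 68 are lost in each arm**

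With 36.5% v 16.7% among the remaining 61:

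- Control: 22.3/68 = 32.7% to 29.3/68 = 43.0%.
- Therapy: 10.2/68 = 15.0% to 17.2/68 = 25.3%.
- Difference as assigned: 7.5 to 28.1 points.

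**The case against.** The strongest reply is that the article never says that dropouts are censored, that their visits stop, or that the primary analysis departs from assigned group. Only the change-from-baseline analyses are limited to children who completed 24 months. Analysis sets and censoring rules are commonly left to an analysis plan, which is not shown. This stands as a limit on the claim: a reader might infer that the comparison is definitely not by assigned group, and the text does not support that. It does not remove the problem. The labelling rules are fixed here, and no later analysis set can recover visits that were not made. Continued visits are offered expressly to irregular therapy users, while nothing equivalent is said for dropped controls or non-starters.

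Second, the deterioration clause can be read more narrowly. A child deviates from a protocol by taking up treatment, not by drifting, and the formal dropout list has no deterioration criterion. That is fair, and it is why the two sections must be reconciled. Nor is the therapy-arm rule an exact mirror, since it is triggered by function tests before training and not by a small exodeviation.

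Third, the largest power losses need children to be dropped before any follow-up visit. A request for therapy could come that early, but observed drift would normally wait for the 6-month visit. The milder column is therefore the more natural one for the deterioration rule.

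Fourth, a reader might infer that the 10% allowance cannot hold. The 20% scenario uses only about 3 to 5 of the 7 places, so the most one can say is that the allowance may be exceeded.

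**Conclusion.** The concern holds in conditional form. The protocol labels randomised children as dropouts by rules that differ by arm and depend on events after randomisation, and one control rule rests on a precursor of the endpoint. Two sections disagree on whether deterioration without treatment is enough. If the label ends follow-up or leads to censoring or exclusion, the primary comparison is informatively censored.

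The size depends on fractions the documents do not give. With 20% to 50% of would-be control failures lost after a scheduled visit, the control estimate falls to between about 33% and 26%, and power from 76% to between about 60% and 27%. If losses can also occur before 6 months, the estimate falls to between about 31% and 21%, and power to between 49% and about 10%. These figures degrade the control arm only. They are not a forecast of the net bias, because loss of non-starters may favour therapy. Controls treated after reaching the endpoint already count as events and are not part of the problem. The matter should be settled before analysis because it bears on the primary randomised comparison.

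**What to change.** - Reconcile Control group therapy with Criteria for dropout, so that one rule states which controls are affected.
- Record uptake of or requests for therapy, sub-threshold deterioration, and failure to start training as protocol deviations, not as reasons to end follow-up.
- Keep every randomised child in the remaining masked visits at 6, 12, 18 and 24 months.
- State that the primary analysis takes all 136 children by assigned group, counts events after crossover, and censors only at loss to follow-up or withdrawal of consent.
- Obtain the remaining visits of children already labelled dropouts where the ±2-week windows are still open, and report the rest as missing.
- Give an analysis censored at crossover, with inverse-probability weights, as a sensitivity analysis only.

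Care decisions are unchanged. The cost is amendment wording and some recall of families. Crossover will dilute the estimate somewhat. Recruitment ran from August 2019 to August 2021 and the article appeared in April 2022, so some missed visits of early enrollees cannot be recovered.

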### Criteria for dropout

The criteria of dropout will be (1) patients in orthoptic therapy group who did not accept training with 2 weeks of enrolment, (2) patients in control group who had started any kind of postoperative non-surgical treatment (e.g., patching, orthoptic training), (3) participants who had requested to be withdrawn from the study. All participants will be permitted to withdraw or terminate the study for any reason during the study, and the reasons will be recorded. Discontinuation or irregular orthoptic therapy will not be a reason for withdrawal from the study, and participants could complete follow-up visits provided if they are willing.

### Patient and public involvement

Before the beginning of this study, we made a survey to the domestic ophthalmologists and optometrists [22]. The survey involved the design of some training program (e.g., time for each training, frequency of hospital training), which facilitated the development of this study. By taking into account of the different learning abilities of patients, we set the difficulty of training program based on the opinions of patients and their parents (or guardians).

### Outcome measurements

Before the beginning of the study, we demonstrated the feasibility of the project, the reliability of the research methods, and the evaluation of the research results. Stereopsis will be checked by the assistant medical staff of the department, and the other binocular vision items and the amount of exodeviation will all be checked by the same senior doctor.

#### Primary outcome

The primary outcomes in our study will be the cumulative proportion of participants meeting suboptimal surgical outcomes at 24 months after surgery; these suboptimal outcomes are defined as (1) exodeviation of ≥ 10 PD at distance or at near using SPCT or (2) loss of 2 octaves or more of stereoacuity from baseline.

#### Secondary outcomes

The secondary outcomes in our study include the following items: the exodeviation at near and distance tested by PACT, fusional convergence amplitude, stereoacuity, accommodative amplitude, and facility.

### Sample size

Sample size calculation is based on the expected value of efficacy from previous studies. The proportion of participants meeting suboptimal surgical outcomes is 16.7% [20] in surgery combined with orthoptic therapy group and 36.5% in surgery alone [21]. We hypothesis that there will be a significant difference in the cumulative proportion of suboptimal surgical outcome at 24 months after surgery between our two groups. We set the statistical power was set at 80% with a type 1 error probability (alpha) of 0.05 based on a 2-tailed chi-square test. The theoretical sample size was 61, with a 1:1 sample ratio. After allowing for a maximum dropout rate of 10% during the 2-year follow-up, we found that the estimated the sample size for each group to reach a statistical significance was 68.

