**Methods:**

A total of 136 IXT patients (aged 7 to 17 years) will be enrolled and assigned to the orthoptic therapy group or blank control group according to a simple randomization scheme. Patients in the orthoptic therapy group will receive at least 2 months of orthoptic therapy, such as anti-suppression, vergence, and accommodation training. Patients in the blank control group will receive only refractive correction. All enrolled patients will need regular follow-up observation until 24 months after surgery. The primary outcome will be the proportion of participants meeting suboptimal surgical outcomes in this 24-month follow-up, which is defined as (1) exodeviation of 10 prism diopters (PD) at distance or near using the simultaneous prism and cover test (SPCT) or (2) loss of 2 or more octaves of stereoacuity from baseline, at any masked follow-up visit examination. The secondary outcomes will be the exodeviation at distance and near using the simultaneous prism and alternate cover test (PACT), magnitude of fusional convergence, stereoacuity, and accommodation. Measurements will be taken at baseline and at the 6-, 12-, 18-, and 24-month follow-ups.

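### The 61 per group does not follow from the stated two-tailed test, which needs 77; it equals the one-sided result, and two-sided power is about 70%, not 80%

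*Protocol article*

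**What the plan says.** All the inputs are in the Sample size section of the protocol article. The expected proportion with a suboptimal surgical outcome is 16.7% with orthoptic therapy and 36.5% with surgery alone. The error rates are given as "We set the statistical power was set at 80% with a type 1 error probability (alpha) of 0.05", and the calculation is "based on a 2-tailed chi-square test". The result is "The theoretical sample size was 61, with a 1:1 sample ratio". The section then raises this figure, "After allowing for a maximum dropout rate of 10% during the 2-year follow-up", to 68 for each group.

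The Abstract (Methods) gives the total: "A total of 136 IXT patients (aged 7 to 17 years) will be enrolled". Since 136 = 2 × 68, the figures 61 and 68 are per group.

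The Statistical analysis section compares the cumulative proportion by two years with the Kaplan-Meier method and adds a between-group difference with a 95% confidence interval. Nothing in the article mentions a one-sided test.

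**The concern.** The difference to be detected is 19.8 percentage points around a mean proportion of 26.6%. For a two-sided 5% test with 80% power, 61 per group looks too few. The article prints every input, so the figure can be checked directly without any outside source.

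The stakes are the power claim for the primary outcome. The article calls the trial large-sample and says that it aims to confirm efficacy. If the trial ends without a significant difference, a reader who trusts the stated 80% will give that result more weight as evidence against orthoptic therapy than the design supports. A second risk is that the sidedness is revisited later to make the printed number correct.

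**Working it through.** **Inputs** (Sample size section): p1 = 0.365 (surgery alone), p2 = 0.167 (with orthoptic therapy), alpha = 0.05, two-tailed chi-square test, power 80% (z = 0.8416), 1:1 allocation, 10% dropout.

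**Quantities derived from them**

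- Difference d = 0.365 − 0.167 = 0.198, so d² = 0.039204.
- Mean proportion = (0.365 + 0.167)/2 = 0.266, so 2 × 0.266 × 0.734 = 0.3905, square root 0.6249.
- 0.365 × 0.635 + 0.167 × 0.833 = 0.2318 + 0.1391 = 0.3709, square root 0.6090.

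**Formula** (pooled variance under the null):

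n per group = [z_α × 0.6249 + 0.8416 × 0.6090]² / d²

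**Reproducing the article's figure**

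- One-sided 5%, z_α = 1.645: (1.0279 + 0.5126)² / 0.039204 = 2.373 / 0.039204 = 60.5, so **61**. This matches the article.
- Dropout: 61/0.9 = 67.8, so **68**. This also matches.

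**The calculation as described**

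- Two-sided 5%, z_α = 1.960: (1.2248 + 0.5126)² / 0.039204 = 3.018 / 0.039204 = 76.99, so **77**.
- Dropout: 77/0.9 = 85.6, so **86** per group, 172 in total. That is 36 more than 136.

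**Could another two-sided formula give 61?**

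| Two-sided method | n per group |
|---|---|
| Pooled | 77 |
| Unpooled | 75 |
| Arcsine | 76 |
| Pooled variance in both terms | 79 |
| Continuity-corrected | 87 |

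None does. The smallest is 14 per group above 61.

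**Power at the planned size**

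Power = Φ[(d√n − z_α × 0.6249) / 0.6090]

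- n = 61, two-sided: (1.5464 − 1.2248)/0.6090 = 0.528, power **70.1%**.
- n = 68, two-sided: (1.6327 − 1.2248)/0.6090 = 0.670, power **74.9%**.
- n = 61, one-sided: (1.5464 − 1.0279)/0.6090 = 0.852, power 80.3%.

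Exact binomial enumeration of the two-sided Pearson test gives 71.3% at 61 and 75.5% at 68. With continuity correction it gives 63.5% and 69.5%.

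**Effect detectable at 61 per group.** With 36.5% in the control group held fixed, two-sided power reaches 80% when the orthoptic proportion is about 14.6%. That is a difference of 21.9 points rather than 19.8.

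**The case against.** Nobody can dispute the arithmetic, but four reservations deserve an answer.

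1. **The one-sided origin is inferred.** The article says two-tailed, and an exact match does not prove what was typed into the software. That stands. The finding does not depend on it, because 61 is wrong for the stated test however it arose.

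2. **The primary analysis is Kaplan-Meier, not chi-square.** This is correct, and it means that 70% is not the exact power of the primary comparison. The printed calculation is still explicitly a chi-square calculation. Changing the method does not close the gap either. Assuming proportional hazards, the stated proportions imply a hazard ratio of ln(0.833)/ln(0.635) = 0.40. Expected events are 61 × 0.532 = 32.5 with 61 per group, or 68 × 0.532 = 36.2 with 68. Two-sided log-rank power is then about 74% (Schoenfeld) or 68% (Freedman) at 61 per group, and about 78% or 73% at 68.

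3. **70% is the worst planned case.** The article calls 10% a maximum, and Kaplan-Meier uses partial follow-up from those who leave early. This is fair, so a range is better than a single figure. Even with full retention the chi-square power is only 75%. Full retention is also optimistic, because the Criteria for dropout section removes control patients who start non-surgical treatment and therapy patients who do not begin training.

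4. **Recruitment is over, nothing is biased, and a confidence interval is already planned.** All true. The error does not distort the estimate or the type 1 error. It concerns what the trial says it can detect, and that can still be corrected.

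**Conclusion.** The concern holds. For the stated inputs the two-tailed test needs 77 evaluable per group, and the article gives 61, which is 16 per group (about 21%) too few. The figure coincides with a one-sided 5% calculation that the article nowhere declares.

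On the planned numbers, two-sided chi-square power is about 70% with 61 evaluable per group and about 75% with all 68. A log-rank analysis gives roughly 68% to 78% across the same two sizes. No uncorrected or log-rank variant reaches 80%, and a continuity-corrected test does worse.

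This takes the article's two proportions at face value; the log-rank figures also assume proportional hazards. The article reports that recruitment is complete but gives no achieved number, so 136 randomised and 122 evaluable (2 × 61) are planned figures.

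**What to change.** Correct the Sample size paragraph, for example:

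> With 136 participants planned and about 122 evaluable after 10% dropout, a two-sided 5% chi-square test has about 70% power to detect 16.7% versus 36.5% (about 75% with no dropout), and 80% power for 14.6% versus 36.5%. For 80% power at 16.7% versus 36.5%, 77 evaluable per group would have been needed.

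Replace the planned numbers with the achieved ones where they are known. Because the primary analysis is Kaplan-Meier, add the corresponding power for that comparison and its assumption.

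Keep the two-sided test. Redefining the test as one-sided so that 61 becomes correct would change the primary inference after recruitment has closed.

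State in advance that a non-significant primary result will be interpreted through the 95% confidence interval for the between-group difference, which the Statistical analysis section already plans, and not as evidence of no benefit.

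The cost is one corrected paragraph and a less favourable stated power. No additional patients and no change to the analysis are required.
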